### Sample size

The appropriate sample size is determined by the non-inferiority approach and was calculated for the primary outcome measure ‘Social Functioning Scale’ [46, 47]. This scale has been used in a subsample of a randomised Housing First trial, from where the necessary data has been taken [48]. For calculating the appropriate sample size of the RCT study site, the application ‘Power and Sample Size’ [49] was used applying the following parameters: Power: 0.9; significance level: 0.025; non-inferiority margin: 15; difference between treatments (group means): 111.2–106.7; standard deviation: 12; and allocation ratio: 1:1. This procedure yielded a sample size of 28 people to be included in each arm.

The OSD sample size is based on the calculation for the RCT. Thus, 28 participants will be included in the treatment arm. For propensity scoring, the many-to-one matching method was chosen. Here, it is recommended to have a 2–3 times larger control group to facilitate matching [50, 51]. Accordingly, 56 to 84 participants will be included in the control group.

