### Participant recruitment

Participants will be recruited between April 2019 and December 2020 within the conventional pathways to gain access to psychiatric residential rehabilitation. At the RCT study site, participants interested in IHS will be consecutively recruited by study collaborators. After agreeing to participate, a study collaborator will explain the purpose and procedures of the study. If the participant gives informed consent, she or he will be subjected to randomisation. For each participant, the result of randomisation is enclosed in an envelope based on a randomisation sheet, which has been calculated before study start for more than 56 consecutive cases. For this calculation, the statistical software R has been used with the procedure for block-randomisation described at [52]. The randomization sheet is saved in a formal study folder only accessible to researchers not involved in the allocation procedure so that no spontaneous modifications can be made during the study enrolment. Subsequently, the treatment condition to which they were randomly assigned will be arranged and the participant is then enrolled. For each measurement point at the RCT study site, participants will receive ten Swiss Francs. The goal of this financial compensation is to minimise potential dropouts in the control group, which have to be assumed due to the strong preference for IHS [32, 33] and the associated difficulties in the enrolment of an RCT [37, 38], especially in the field of supported housing [4].

At the OSD study site, participants will be consecutively recruited by residential rehabilitation staff or by social workers at the mental health hospital they are discharged from. After being admitted to the respective treatment condition, a study collaborator will ask them to give informed consent. Consenting participants will be subsequently enrolled into the observational study.

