### Interventions

The study intervention called Independent Housing and Support (IHS) is a psychosocial residential rehabilitation programme and means direct placement of people with SMI in accommodation in the community, i.e., without prior housing arrangements. This complex intervention follows the “First place – then train” paradigm which is well-known from Supported Employment within vocational rehabilitation. The accommodation is usually a flat rented at service user’s choice, and is financed at their expense. The service user will be supported by an off-site residential coach concerning all aspects related to finding and keeping his or her accommodation, including contacts with the landlord, social environment, relatives, and administration. The residential coach will not be in charge of any issue related to treatment or therapy, but will cooperate with the service user’s psychiatrist or psychiatric service. The intensity of residential coach support will be flexible and according to the service user’s needs. IHS is not transitional, but permanent and without time limitation and is independent of therapy or care. The main goal is the social inclusion of service users.

The control condition RCS/TAU consists of traditional residential care settings (RCS) such as staffed or unstaffed care homes, shared or non-shared apartments rented by the residential agency, and other treatment as usual conditions (e.g. host families, unsupervised living). RCS settings are part of a continuum of residential services other than hospital for non-acute support that aim to enable the individual with SMI to live independently. Users live in a group in a single or shared room, and receive daily support on-site or at least 7 h per day and at least on 5 days per week. If there is no continuous support on-site, users get 24 h on-call support. The hiring contract is concluded with the residential agency. In some of the RCS settings, there is the expectation that users will move on within two years. Closed residential settings or traditional housing settings not fulfilling the above criteria will be excluded from the present study.

As both study conditions are part of psychiatric rehabilitation not providing any acute psychiatric care, temporary inpatient or outpatient stays in a (mental) hospital are seen as common and will neither affect their utilisation of the rehabilitation setting nor their participation in the study.

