### Outcome assessment and measures

Participants will be followed for two years after enrolment. Outcome assessments take place at baseline (T0), after 6 months (T1), 12 months (T2) and after 24 months (T3). Data will be collected by interview with participants as well as by self-report questionnaires answered by participants in a paper-pencil format. Assessments with participants will be conducted by trained assessors at the participants’ accommodation or another place of their choice. Model fidelity as well as the costs of RCS/TAU will be assessed by interview with heads of each of the utilised residential rehabilitation service.

Social inclusion will be assessed as the primary outcome as the main goal of residential rehabilitation approaches is the social inclusion of individuals with SMI. Secondary outcomes include functioning, quality of life, mental state, diagnoses, needs, capabilities, life events, social support, service utilization and costs. Participants’ diagnoses as well as contact frequency in IHS settings are collected from clinical records. All outcome measures will be assessed with a German version of the corresponding measures.

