### Primary objective: care-related goal

For analysing the primary outcome variable social inclusion we will check for non-inferiority both in per-protocol and in imputed ITT samples to assess the security of inference of non-inferiority as recommended in the CONSORT guidelines for non-inferiority trials [72, 73].

Primary analysis will compare primary and secondary outcomes between IHS and RCS/TAU after 6, 12 and 24 months separately for both study sites. A repeated measure approach will be used where indicated. Non-inferiority of IHS compared to RCS/TAU will be accepted based on a 2.5% significance level if the lower bound of the 97.5% CI of M_IHS_-M_RCT/TAU_ is > δ = − 15, and vice versa, non-inferiority of IHS compared to RCS/TAU cannot be accepted if the lower bound of the 97.5% CI of M_IHS_-M_RCT/TAU_ is ≤ δ = − 15. This non-inferiority margin corresponds to one standard deviation of 15 scale scores (*m* = 100; *SD* = 15) on the primary outcome variable SFS [46, 47] and was chosen based on the clinical judgment of experts as no RCT investigating the SFS as outcome measure in a comparable sample was available [81]. In addition, assay sensitivity will be analysed by investigating pre-post differences in a first step. Assay sensitivity will be assumed, if there is a statistically and clinically significant pre-post increase in the SFS total scale score [82].

All other outcome measures will also be tested on their non-inferiority using the definition of margin δ as one standard deviation of the respective scale. Analyses will be extended to superiority testing in case of confirmed non-inferiority, and to interaction terms to explore mechanisms of treatment effects.

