### Limitations

There are some limitations possibly compounding the interpretation of the findings. Firstly, most of the measures were assessed based on self-reported answers of participants, which can differ from more objective views. Therefore, the key workers ratings of participants’ functioning will be also assessed. Where necessary, key workers will be supported in doing the ratings by study collaborators. Secondly, blinding of participants or study collaborators is not possible due to the housing nature of the investigated conditions. Thirdly, the current study proposes a pragmatic non-inferiority hypothesis because there was no former study investigating our primary outcome variable *Social Functioning Scale* (SFS) [46, 47] in a comparable service field. Therefore, a historical justification of the non-inferiority margin δ and of an assay sensitivity as is usually recommended in non-inferiority trials [72, 73] was not applicable. Nevertheless, proposing a superiority hypothesis would not be appropriate for the present research because of the mixed results in comparative effectiveness research regarding residential rehabilitation in non-homeless people with SMI [16, 19–22]. Furthermore, the sample size calculation is based on the primary outcome measure, therefore, the present study has possibly not included enough participants to detect statistical significant differences in secondary outcomes tested on superiority of IHS. Accordingly, analyses on secondary outcomes have to be interpreted in an exploratory manner. It is important to recognise that the failure to find a difference does not imply non-inferiority regarding the respective outcome variable [83]. And last but not least, the study is conducted as a field study in two separate service areas. Therefore, the generalisability to other regions or other service providers may be limited.

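### A pre-post rise in SFS cannot establish assay sensitivity, so a positive non-inferiority result should not be read as if it had been shown

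*Protocol article*

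**What the plan says.** The section on the primary objective accepts non-inferiority if the lower confidence bound for IHS minus RCS/TAU on the SFS lies above −15. It then adds that "assay sensitivity will be analysed by investigating pre-post differences in a first step", and gives the criterion: "Assay sensitivity will be assumed, if there is a statistically and clinically significant pre-post increase in the SFS total scale score". The criterion uses change from baseline and no contrast between conditions. The article describes no later step.

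The Limitations section says that "a historical justification of the non-inferiority margin δ and of an assay sensitivity as is usually recommended in non-inferiority trials" could not be given here, because the SFS had not been studied in a comparable service field. It does not list the pre-post criterion itself as a limitation.

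The Interventions section defines the control as residential care settings plus "other treatment as usual conditions (e.g. host families, unsupervised living". There is no separate untreated arm. Assessments are at baseline and at 6, 12 and 24 months (Outcome assessment and measures).

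**The concern.** Assay sensitivity is the ability of a trial to show a difference between an effective and a less effective condition when one exists. It is a property of the comparison. A within-group rise mixes any housing effect with three things that have nothing to do with housing: recovery over time, regression to the mean in people who enter when they need support, and repeated assessment. The documents make the first plausible at the observational site, where participants are recruited "by residential rehabilitation staff or by social workers at the mental health hospital they are discharged from".

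At stake is what a positive result is taken to mean. Two equally ineffective settings would give similar SFS means and would easily pass a 15-point margin. An assay-sensitivity argument is meant to guard against reading that result as evidence that both settings work. With no historical evidence available, the pre-post rule is the only support the article offers, and it cannot do this job.

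**Working it through.** **Inputs from the article (Sample size; Primary objective).** Margin 15 ("This non-inferiority margin corresponds to one standard deviation of 15 scale scores"); SD 12; group means 111.2 and 106.7, so a difference of 4.5; "Power: 0.9; significance level: 0.025"; 28 per arm, 56 in the RCT.

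**The plan's own figure.** With alpha 0.025 one-sided and the 4.5-point difference taken off the margin:
n per arm = 2 × [12 × (1.960 + 1.282) / (15 − 4.5)]² = 27.45, rounded up to 28. It reproduces, so the sample size arithmetic is not in dispute.

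**Assumptions not in the article.** Pre-post correlation r = 0.6 (range 0.3 to 0.7); natural rise of 3, 5 or 6 points with no effect of either setting; a two-sided 5% paired test on all 56 participants; a clinical threshold of 5 to 15 points applied to the mean change.

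**Step 1, the statistical half of the rule.**
- SD of change = 12 × √[2 × (1 − 0.6)] = 10.73.
- Standard error with 56 participants = 10.73 / √56 = 1.434.
- Smallest significant observed rise = 2.004 × 1.434 = 2.87 points.
- Probability of significance from the noncentral t distribution: 53.8, 92.8 and 98.4% for natural rises of 3, 5 and 6. With 28 participants: 29.7, 66.2 and 81.4%.
- For a 6-point rise with 56 participants, r from 0.3 to 0.7 gives 87.4 to 99.7%.

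**Step 2, the full rule.** The criterion also requires clinical significance. Every threshold below exceeds 2.87 points, so the threshold is the binding part, and the probability is approximately 1 − Φ[(threshold − rise) / 1.434].

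| Assumed threshold | Rise 3 | Rise 5 | Rise 6 |
|---|---|---|---|
| 5 | 8% | 50% | 76% |
| 7.5 | 0.1% | 4% | 15% |
| 10 | <0.1% | <0.1% | 0.3% |
| 15 | 0% | 0% | 0% |

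Example: rise 6, threshold 5 gives (5 − 6) / 1.434 = −0.70, and 1 − Φ(−0.70) = 0.76.

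**Step 3, can the rule tell an effect from no effect?** Mean change equals natural rise plus housing effect, and the rule sees only the sum. In 20,000 simulated trials (28 per arm, r = 0.5, threshold 5) it was met in 74% when both settings were inert with a 6-point natural rise. It was also met in 74% when both had a true 6-point effect and there was no natural rise. This holds at any threshold, because the two cases give the same distribution of change.

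**Step 4, alongside the non-inferiority test.** With both settings inert, the standard error of the difference is 12 × √(2/28) = 3.21, and the lower bound clears −15 in about 99.6% of trials. In the simulation the rule and non-inferiority were met together in about 73% of trials (natural rise 6, threshold 5).

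**The case against.** The strongest reply is that the rule asks for clinical as well as statistical significance, and that a demanding threshold would stop natural recovery from meeting it. This stands as far as it goes. A reader might infer from the 54, 93 and 98% figures that natural recovery would usually satisfy the rule. The article does not support that: it gives no natural SFS gain, no correlation and no threshold, and the answer runs from 76% to nil depending on the threshold. But a higher threshold only makes the rule harder to meet. It does not make it a measure of discrimination between conditions.

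A reader might also infer that the rule produces false declarations of non-inferiority. It does not: acceptance rests on the confidence bound alone, so neither the decision nor its type I error is affected. Nor does the article say that a trial without a rise would be discounted.

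The case for recovery is also limited. Discharge from hospital is named only for the observational site, as one of two recruitment routes, and the eligibility criteria exclude people who need hospital treatment for acute symptoms at admission. Unsupervised living is one example within usual care, with no share given, so it does not show that both arms are ineffective.

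The article is open about the missing history, plans both per-protocol and imputed ITT analyses, and already words its hypothesis as IHS giving no poorer outcomes than RCS/TAU. The arm, time point, threshold and any second step may stand in an analysis plan not shown, and their absence is not held against the article. None of this supplies a comparator for the pre-post rise.

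**Conclusion.** The point holds as a matter of interpretation. The stated criterion cannot support the inference drawn from it, and this does not depend on any numerical assumption: change from baseline carries no information on how much of it is due to housing. The numbers show only that the criterion could be met with no housing effect, in about 8, 50 or 76% of trials for natural rises of 3, 5 or 6 points and a 5-point threshold, and in 0.3% or less from 10 points upward (SD 12, r = 0.6, 56 participants). Natural rise, correlation and threshold are assumptions. It would go too far to say that natural recovery alone would meet the rule, or that the non-inferiority decision is invalid. The text should be changed, because the rule is the only support offered for assay sensitivity and it bears on what the trial may conclude.

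**What to change.** Remove the sentence that assumes assay sensitivity from pre-post change. Report within-arm SFS change descriptively. State that assay sensitivity is unverified, in line with what the Limitations section already concedes about history. Word a positive conclusion as not worse than the RCS/TAU mix by more than the margin, not as evidence that either setting is effective.

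As context, use data already planned: the fidelity scores in both conditions, and the type of housing actually used over follow-up, which the service-use inventory covers through its item on whereabouts. Contact data can be described for IHS only. The reimbursement tool that records them is not used by RCS/TAU services, whose heads are asked only for costs, so no between-arm comparison of contact intensity is available.

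The cost is wording in the analysis plan and the report, with no new data and no change to the sample size. The downside is a more modest claim.

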### Secondary objective: methodological goal

In order to analyse the secondary objective of methodology, descriptive homogeneity testing will be conducted to evaluate whether RCT data and OSD data can be pooled to be subsequently analysed jointly. If so, the analyses related to the care-related objective described above will be repeated with the pooled data from both study centres.

## Discussion

There is a strong preference in service users for independent living but a considerable lack of research into housing services in the context of mental health. In this prospective, four-arm cohort study we aim to evaluate the effectiveness and efficiency of Independent Housing and Support (IHS) compared to institutionalised residential care settings and other treatment as usual conditions (RCS/TAU) for people with SMI in two cities in Switzerland. Effectiveness will be assessed by social inclusion and related outcomes while efficiency will be analysed by service usage and costs testing hypotheses of non-inferiority. Participants will be enrolled between April 2019 and December 2020 and assessed at baseline, after six, twelve and after 24 months. At one study site, 56 participants will be randomly assigned to one of the conditions; the other study site will use an observational study design including 112 participants.

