**Discussion:**

While the UN Convention of the Rights of People with Disabilities aims to promote the opportunity to choose one’s place of residence, the limited supply of alternative forms of housing does not guarantee genuine freedom of choice. Increased diversification and flexibility of housing support is essential. If IHS shows non-inferiority in terms of their effectiveness and efficiency, users should be allowed to choose their kind of housing support.

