## Methods

### Aims of the study

Based on these findings, we aim to investigate both 1) a care-related and 2) a methodological goal with the current multi-centre study to answer the following research questions:
What are the effectiveness and efficiency of IHS compared to RCS/TAU for non-homeless persons with severe mental illness after 6, 12, and 24 months?Do the RCT and the OSD yield similar results?

The primary objective is to evaluate the effectiveness and efficiency of IHS and to directly compare it to traditional RCS/TAU for non-homeless people with severe mental illness. Effectiveness will be determined by social inclusion, proposed as a key outcome for individuals living with mental disorders and, in terms of research, a global priority measure [45]. Efficiency will be analysed based on the costs associated with the service utilization of the different housing settings. As the political goal is seen in allowing a freedom of choice in where to live and which support services to utilise [3] and because the differences in outcomes of previous studies between IHS and RCS for non-homeless populations were only small or inexistent [16, 19–22], we utilise a non-inferiority hypothesis in our study. We hypothesize that IHS yields no poorer social inclusion outcomes than traditional RCS/TAU.

One study centre is going to conduct an OSD with propensity score matching methods and the other center plans to conduct an RCT while learning from the results of the recently failed feasibility trial of IHS [4]. Thus, to our knowledge, the present study will include the first RCT investigating housing conditions for non-homeless people with SMI. The secondary objective of this study is to directly compare the outcomes of the RCT with the OSD. Here, we utilise the hypothesis that the OSD will provide similar results to the RCT. If the hypothesis is confirmed, observational studies investigating residential rehabilitation programmes for the non-homeless population could be considered as equivalent to the RCTs so far solely conducted with respect to homeless people.

In addition, we will conduct secondary analyses to investigate the moderation, mediation and procedural factors in IHS and RCS/TAU that influence outcomes.

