#### Service utilisation

The evaluation of the German adaptation of the *Client Sociodemographic and Service Receipt Inventory* (CSSRI-EU) [61] proved its feasibility in assessing utilisation of mental health care in Germany. A study-specific adaptation to mental health care and residential rehabilitation settings in Switzerland (CSSRI-CH) will be used to measure costs and utilization of psychiatric services. The nine items ask participants for 1) their main source of income, 2) their net income in Swiss Francs, 3) their whereabouts in the last 12 months, 4) any health care utilisation for physical health problems and 5) for mental health problems, 6) any intake of psychotropic medication, 7) contact with criminal justice services, 8) internet access, and 9) any other support utilised. Evaluation will be conducted in a descriptive manner.

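### Efficiency is promised a non-inferiority conclusion, but the cost and service-use instrument is evaluated descriptively, and the only margin that reaches costs (one SD of the scale) does not suit them

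*Protocol article*

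**What the plan says.** All references are to the protocol article.

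- **Discussion (opening paragraph):** "efficiency will be analysed by service usage and costs testing hypotheses of non-inferiority".
- **Abstract, Discussion:** "If IHS shows non-inferiority in terms of their effectiveness and efficiency, users should be allowed to choose their kind of housing support".
- **Aims of the study:** efficiency is part of the primary objective: "Efficiency will be analysed based on the costs associated with the service utilization of the different housing settings". The hypothesis stated there covers social inclusion only: "We hypothesize that IHS yields no poorer social inclusion outcomes than traditional RCS/TAU".
- **Service utilisation:** the CSSRI-CH "will be used to measure costs and utilization of psychiatric services", and the section closes with "Evaluation will be conducted in a descriptive manner".
- **Service provision and costs:** IHS contacts and costs come from the TARMED reimbursement tool. RCS/TAU costs come from one question to the head of each service about its daily or weekly rate. No analysis of these costs is described.
- **Outcome assessment and measures:** "Secondary outcomes include functioning, quality of life, mental state, diagnoses, needs, capabilities, life events, social support, service utilization and costs".
- **Primary objective: care-related goal:** all outcomes other than the SFS are also to be tested for non-inferiority, "using the definition of margin δ as one standard deviation of the respective scale".
- **Limitations:** the sample size rests on the primary outcome, and secondary outcomes are to be read as exploratory.

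**The concern.** For service use, and for the costs captured by the CSSRI-CH, the plan gives two incompatible instructions: test for non-inferiority, and evaluate descriptively. A descriptive evaluation tests no hypothesis, so both cannot be followed.

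If the testing instruction prevails, the only margin available is one SD of the scale. That has a fixed meaning for the SFS, whose scale scores are normed to a mean of 100 and an SD of 15. Costs have no such norm. Either the margin is undefined, or it is taken from the sample, so that more variable costs make non-inferiority easier to claim. The two arms' housing costs are also recorded differently (contact records against a service-level rate), which makes their joint spread a poor basis for a margin.

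At stake is the efficiency half of the primary objective and the Abstract's policy sentence, which requires non-inferiority on both counts.

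**Working it through.** **1. The plan's own sample size.** Inputs from the Sample size section: margin 15, SD 12, group means 111.2 and 106.7 (difference 4.5), significance level 0.025, power 0.90, allocation 1:1. With the difference taken against IHS and a one-sided test:

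n = 2 × (1.960 + 1.282)² × 12² / (15 − 4.5)² = 2 × 10.51 × 144 / 110.25 ≈ 27.5, hence 28 per arm.

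The stated 28 reproduces. It is sized on the SFS alone; no calculation covers costs.

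**2. Which rule reaches costs.** Service utilisation and costs are listed as secondary outcomes. The margin rule covers all outcomes other than the primary and names no exemption. No other cost margin is given.

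**3. What the rule would do with a sample SD (RCT, 28:28, one-sided 0.025).** Working in SD units:

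- SE = √(1/28 + 1/28) = 0.267
- Largest observed excess that still passes = 1 − 1.96 × 0.267 = 0.48 SD
- Probability of passing at a true excess d = Φ((1 − d)/0.267 − 1.96)

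| True IHS cost excess (SD) | Probability of declaring non-inferiority |
|---|---|
| 0 | 96% |
| 0.25 | 80% |
| 0.5 | 46% |
| 0.75 | 15% |
| 1.0 | 2.5% |

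**4. In terms of mean cost.** The document gives no cost SD, so the coefficient of variation (CV) is an assumption. The largest passing excess is CV × 0.476.

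| Assumed CV | Margin, % of mean cost | Largest observed excess that passes, % of mean cost |
|---|---|---|
| 0.5 | 50 | 24 |
| 1.0 | 100 | 48 |
| 1.5 | 150 | 71 |

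**5. Sensitivity.** If the 97.5% interval in the decision rule is read as two-sided (one-sided 0.0125), the largest passing excess at 28:28 falls to 0.40 SD, and a true excess of 0.5 SD passes about 36% of the time. At the observational site, ignoring the matching, the largest passing excess at one-sided 0.025 is 0.55 SD for 28:56 and 0.57 SD for 28:84. The picture does not change.

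**The case against.** Much can be said for the plan.

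- **The margin rule may not be meant for costs.** It speaks of scales, and the list of secondary outcomes also contains diagnoses and life events, which cannot sensibly take a scale-SD margin. This is a fair reading. But then no margin for costs exists in the document, while the Discussion still promises a non-inferiority test of them. The problem changes form but remains.
- **An a priori analysis plan is mentioned and may deal with costs.** A detailed cost analysis could well be left to it. What the article already fixes is another matter: it says both test and describe, and it sets one margin for every other outcome. A later plan could repair this only by departing from the published text.
- **Secondary analyses are declared exploratory.** This answers any complaint about missing power for costs. It does not fit with an Abstract that makes efficiency a condition for a policy recommendation.

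Four stronger readings are tempting and are not supported:

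- *All cost data are evaluated descriptively.* The descriptive sentence belongs to the CSSRI-CH. For housing-service costs the analysis is simply unstated.
- *IHS could cost one full SD more (50% to 150% of mean cost at the assumed CVs) and be accepted.* The confidence bound, not the estimate, must clear the margin. A true excess of one SD would pass only about 2.5% of the time, and the observed limit is about half the margin.
- *The rule yields a wrong verdict, or no conclusion is possible at all.* A sample-SD test could be run mechanically; its result would just say little about efficiency.
- *The lower-bound decision rule fails because lower costs are better.* That rule is written for the SFS. HoNOS and SCL-K-9 also run in the lower-is-better direction, and reversing the sign is routine.

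**Conclusion.** The point stands as an internal contradiction joined to an unsuitable rule. Service use and CSSRI-CH costs are both to be tested and to be described; housing-service costs have no stated analysis; and the one margin that reaches any of them is undefined for costs or set by the sample's own spread. In the latter case, at 28 per arm, the test tolerates an observed excess of about 0.48 SD and passes nearly half the time when IHS truly costs 0.5 SD more. A pass would not carry the Abstract's efficiency statement.

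The SD-unit figures rest on the plan's arm size, one-sided 0.025, a normal approximation and the sample SD as margin. The percentages of mean cost (24% to 71%) rest in addition on the assumed CV of 0.5 to 1.5. The SFS analysis, its margin and the sample size are not touched. The matter should be corrected because it changes what the trial may claim on efficiency.

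**What to change.** 1. Remove efficiency from the non-inferiority claims in the Abstract and in the opening paragraph of the Discussion.
2. In the section on the care-related goal, exempt costs and service use from the one-SD margin.
3. Align the Service utilisation section with this, so that one instruction applies, and state the analysis for housing-service costs.
4. Report the difference in mean cost per participant (IHS minus RCS/TAU) by site at 6, 12 and 24 months with a bootstrap 95% confidence interval. At the observational site, resample in a way that respects the matched sets. Note that RCS/TAU housing costs are service-level rates shared by residents, so resampling participants alone does not capture uncertainty between services.
5. Label the result exploratory, in line with the Limitations section.

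The cost is a few changes of wording and one further analysis of data already planned. The downside is a weaker efficiency claim. The interval will also be wide: at 28:28 its approximate half-width is 1.96 × 0.267 = 0.52 SD, or about 26% to 79% of mean cost at the assumed CVs. That imprecision is better shown than hidden behind a one-SD verdict.
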